## Statistical analysis

3

Statistical analysis was performed using SPSS Statistics 26.0 software. Count data were expressed as a number of cases and rate (%). The distribution of continuous data will be tested for normality, and information conforming to normal distribution will be expressed as mean ± standard deviation (M ± SD), and non-normal information will be expressed as median (IQR). The Mann–Whitney U test will be used to compare the change in scale scores between baseline and endpoint between the two groups, and the Wilcoxon test will be used to compare the difference in scale scores between baseline and endpoint between the two groups. The chi-square test will be used to compare the demographic characteristics of the two groups. A two-sided test will be used and will be considered statistically significant if *p* < 0.05.

Assuming a reasonable amount of missing data, the data summary will indicate that data are missing at random. In this case, all analyses will be performed with the baseline variable as the auxiliary variable, the missing data will be supplemented by multiple interpolation procedures, linear regression and logistic regression will be selected for the analyses, and the final combined analyses will be performed to complete the process of interpolation and analysis.

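### Two rank tests are assigned to one between-arm comparison of scale scores, and the pooled regressions named for imputed data are not reconciled with them

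*Protocol article*

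**What the plan says.** Protocol article, section 3 (Statistical analysis), first paragraph: "The Mann–Whitney U test will be used to compare the change in scale scores between baseline and endpoint between the two groups", and in the same sentence "the Wilcoxon test will be used to compare the difference in scale scores between baseline and endpoint between the two groups". Which Wilcoxon test is meant is not stated. Neither test is described as adjusted for baseline.

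The second paragraph deals with missing data. It states that "all analyses will be performed with the baseline variable as the auxiliary variable", that "the missing data will be supplemented by multiple interpolation procedures" (evidently multiple imputation), that "linear regression and logistic regression will be selected for the analyses", and that "the final combined analyses will be performed to complete the process of interpolation and analysis". It does not say how these regressions relate to the rank tests of the paragraph before.

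Three other places bear on the point. Section 2.7 lists the scales as secondary outcomes and TSH as primary. Table 2 in section 2.8 shows every scale and hormone measured at baseline, 3 and 6 months. Section 2.3 allows for 20% loss.

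**The concern.** The two halves of the sentence on rank tests describe one contrast: arm against arm, on baseline-to-endpoint change. A plan that gives two tests for one contrast either repeats itself or uses a test that cannot answer the question. If the second is a signed-rank test run in each arm, its p-values say whether each arm changed, not whether the arms differ. Because the text presents it as a between-group comparison, such p-values could be offered as evidence of effect.

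The missing-data paragraph adds a second route. With 20% loss planned for, the imputed-data analysis will matter. Results could come from a rank test on observed data or from a pooled regression on imputed data, and the plan does not say which one leads. Section 3.1.1 adds that experts will be consulted on the choice of methods at the analysis stage, so nothing else in the article settles it beforehand.

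The third issue is efficiency. Baseline values are collected for every scale and hormone, yet baseline is named only as an auxiliary variable in the missing-data paragraph and not as a covariate of the tests.

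**Working it through.** **The plan's own figure.** Section 2.3: achievement 90% against 60%, two-sided 0.05, power 90%. With unpooled variance, n = (1.960 + 1.282)² × (0.9×0.1 + 0.6×0.4) / 0.3² = 38.53, so 39 per arm. Allowing for 20% loss, 39/0.8 = 48.75, so 49 per arm and 98 in total. This agrees with the plan. It rests on a binary TSH rate and does not depend on how scale scores are tested.

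**What the Wilcoxon test can be.**
- Rank-sum: the same test as Mann–Whitney. On a simulated data set with 39 per arm, both gave p = 0.0795.
- Signed-rank: a paired test of time points within an arm, with no comparison of two independent arms.

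Under neither reading is the sentence right as written.

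**What happens if within-arm tests are read as a comparison.** Assume the same true change in both arms and 39 per arm (2,000 simulated trials). One arm is significant and the other is not in 49% of trials when the true change is 0.3 SD of the change score, 44% at 0.4 SD and 27% at 0.5 SD. The effect sizes are assumptions; the protocol gives no expected change in the scales.

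**Rank tests and imputation.** Section 3 allows two readings of the regressions.
- They are the analysis models. They then compete with the rank tests, and no order is given.
- They are the imputation models. The rank tests are then the analysis, but as named they come with no estimate and standard error to combine over imputations.

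Both readings leave the two paragraphs unreconciled.

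**Efficiency of baseline adjustment.** With equal SD σ at baseline and follow-up, and correlation r between them:
- variance of a change score: 2σ²(1 − r)
- residual variance after linear adjustment for baseline: σ²(1 − r²)
- ratio: 2(1 − r)/(1 − r²) = 2/(1 + r)

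The protocol gives no r, so a range is shown. The simulated power is for 39 per arm, normal data, an assumed effect of 0.65 SD and 3,000 runs.

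| Assumed r | Variance ratio 2/(1+r) | Power, Mann–Whitney on change | Power, ANCOVA |
|---|---|---|---|
| 0.3 | 1.54 | 64% | 84% |
| 0.5 | 1.33 | 78% | 90% |
| 0.7 | 1.18 | 95% | 98% |

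At r = 0.8 the simulated powers are 99% and 100%. The loss is clear at r of 0.5 or below and small from 0.7 upwards.

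**The case against.** Much can be said for the plan.

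- **Mann–Whitney on change is a valid test** in a randomised trial. Several scales are short and bounded (PHQ-4 from 0 to 12, ARMS-7 from 7 to 28), so a rank test is defensible. This stands: the fault is lost efficiency, not an inflated error rate.
- **The rank tests are stated only for scale scores**, which are secondary. A reader might infer that the primary TSH comparison is mis-specified. The text does not support that: linear and logistic regression suit continuous TSH and the TSH rate, and further detail may lie in a fuller document.
- **A reader might turn the variance ratio into patients wasted, or into a wrong sample size.** Neither follows. The ratio compares mean-based estimators under equal variances, not a rank test on bounded ordinal scores, and the sample size rests on a binary rate.
- **A reader might say that change scores or rank methods can give no effect estimate, or cannot be pooled.** That goes too far. A difference in mean change has a confidence interval, and so does a Hodges–Lehmann shift. The fair point is that section 3 names no such estimate.
- **The Wilcoxon clause may be a slip of wording** for a within-arm test. That is likely, and nothing shows that its p-values would be reported as a treatment effect. One could argue that both arms will change because both receive hormone therapy, but that argument fits TSH better than the scales.

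What remains is the wording of the Wilcoxon clause, the lack of an order between rank tests and regressions, and an avoidable loss of precision.

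**Conclusion.** The point holds in a limited form and should be fixed. As written, section 3 gives two tests for one between-arm contrast, and one reading of the second cannot compare arms at all. It then names pooled regressions on imputed data without saying whether they or the rank tests are the main analysis. These are faults in what the text states, not details left for later.

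The efficiency part depends on r, which is not given: it is material at moderate or low correlation and minor at 0.7 or more. It assumes equal variances and mean-based analyses, and the simulation assumes normal data. The validity of Mann–Whitney and the 49 per arm are not in question.

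**What to change.** Rewrite the methods paragraphs of section 3 so that each outcome has one named between-arm analysis, the same in observed and imputed data:

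- **Scale scores, hormones and log TSH:** linear regression of the follow-up value on arm and baseline value.
- **TSH achievement rate:** logistic regression on arm and log baseline TSH. At the design rates, 39 × 0.10 + 39 × 0.40 = 19.5, so about 20 non-achievers among 78 completers, which should support a model with these two terms.
- **Missing data:** multiple imputation with arm in the imputation model, and estimates pooled by Rubin's rules. State which regressions are imputation models and which are analysis models.
- **Signed-rank test:** if kept, label it within-arm and descriptive, not evidence of effect.
- **Mann–Whitney on change:** keep it as a sensitivity analysis for the ordinal scales.

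The cost is a rewritten paragraph, with no new data, since all baseline values are already collected. The downside is some added modelling assumptions for short bounded scales, which the Mann–Whitney sensitivity analysis covers.

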### Study management

3.1

#### Data collection

3.1.1

Prior to the commencement of the study, the investigator will be fully trained and assessed. The investigator will need to ensure that all study results, including clinical and laboratory data, will be recorded in a pre-made subject registration form so that study subjects can be enrolled and coded to minimize the incidence of missed visits during follow-up. To maintain consistency between the intervention and control groups, survey times and questionnaires will remain essentially the same. The investigator will need to ensure that all sections of the registration form are entered correctly and that each completed patient’s data must be dated and signed to ensure that the trial can be validated retrospectively based on the data once completed. During subsequent data analysis, a double-checking procedure will be implemented to improve the quality of data entry, and experts will be consulted to select appropriate statistical methods.

#### Storage and archiving of data

3.1.2

Investigators are required to archive all trial data (list of subject identification codes, source data, and investigator files) and related correspondence in study-specific database files. All source data for the database and all related documentation for the study will be archived in accordance with laws and regulations after the trial is finalized.

#### Ethics and regulations

3.1.3

The procedures set out in this trial protocol relating to the conduct, evaluation and documentation of this trial are designed to ensure that all participants in the trial adhere to the ethical principles described in GCP and the current revision of the Declaration of Helsinki. The trial will be conducted in accordance with the requirements of local laws and regulations, and approval for this trial protocol was obtained from the Ethics Committee of the Fourth Hospital of Harbin Medical University (2022-WZYSLLSC-20).

#### Ethics committee

3.1.4

For quality assurance, this trial will comply with ethical and legal requirements and the trial will have to inform the Ethics Committee of all subsequent protocol revisions that require formal approval in accordance with local legal requirements. The Ethics Committee will have to be informed in advance of the trial procedures, if not specified more in the documentation. The Ethics Committee will have to be informed of the end of the trial at the end of this trial.

#### Informed consent

3.1.5

Prior to undergoing the trial, patients will have to voluntarily agree to participate after an explanation of the nature, scope and possible consequences of this trial. Informed consent must be obtained from each individual patient or their legally authorized representative prior to the start of the trial. Patients who are unable to sign but are able to understand the significance of participation in the study may give verbally witnessed informed consent. These patients must clearly demonstrate that they are willing to participate voluntarily and must be able to understand an explanation of the contents of the informed consent form.

#### Confidentiality

3.1.6

Authorized consent to use their trial data must be obtained from the patient prior to enrollment. To protect patient privacy, the patient’s age will be recorded on the registration form without recording the patient’s year of birth, and the name will be replaced by a cell phone number. During the trial, trial results stored on computers will be stored in accordance with local data protection laws and will be handled in strict confidentiality. The investigator will implement organizational procedures that set access rights to the files to prevent data from being sent to unauthorized persons. Appropriate provisions of local data regulations will be fully complied with. Authorized personnel may inspect subject-related data collected during the trial to ensure that the data are legally protected.

#### Investigator responsibilities

3.1.7

Prior to the start of the trial, the trial protocol, informed consent document and any other appropriate documentation will be presented to the independent study team members. The study leader and principal investigator will regularly supervise the study implementers to ensure that all study procedures are being carried out correctly and that the data collected are accurate. Each investigator should ensure that all personnel assisting with the trial are fully informed about the protocol, any modifications to the protocol, the trial treatment, and their duties and functions related to the trial.

#### Approval of trial protocol and amendments

3.1.8

If the investigator fails to comply with the pre-established survey and follow-up criteria, the study leader will retain the authority to terminate the trial, revise the randomization protocol, and re-collect the data after the revisions have been completed. In the event of fundamental or widespread design errors or inaccuracies in the study questionnaire during the course of the investigation, the investigator will discontinue the trial and revise and redesign the questionnaire. After the necessary revisions have been completed, the revised questionnaire will be redistributed to patients.

#### Data monitoring

3.1.9

The Data Monitoring Committee (DMC) will consist of at least two members from the Medical Ethics Committee of the Fourth Affiliated Hospital of Harbin Medical University, who must not have a conflict of interest with the investigators of the project. The DMC will monitor and review the study on a regular basis and report the results to the Ethics Committee. This process will be independent of the principal investigator. The DMC will have the right to suspend or terminate the study if they find any deviation from the approved study protocol or any unauthorized changes in the study procedures during the course of the study.

#### Safety

3.1.10

All adverse events (SAEs) or adverse events (AEs) reported by the patient or detected by the investigator will be collected during the trial and must be recorded on the appropriate page of the registration form. All SAEs and AEs that occur after the patient has signed the informed consent document will be recorded on the page of the registration form. All patients with SAEs and AEs, whether or not considered relevant to the trial, must be monitored to determine outcomes. This trial will have to be reported to the primary study leader within 24 h of the SAE and AE occurring. The initial report must be as complete as possible, including details of the (serious) SAE and AE in the current trial and an assessment of the causal relationship between the event and the trial and the occurrence of the event. The Principal Study Leader will notify the Trial Supervisor of serious SAEs on request and also has a responsibility to report any serious SAEs or AEs to the Ethics Committee in a timely manner.

## Discussion

4

The great leap forward in the information age has broken the information gap between “medical” and “personal” for centuries. Obtaining personalized medical knowledge and information through the mobile Internet is an essential skill in this era, and therefore mHealth is rapidly developing. mHealth can be thought of as a healthcare that uses mobile communication devices as a carrier, and supports the long-term sustainability of healthcare by improving effective communication between doctors and patients and the patient’s understanding of the disease based on online communication channels, such as video, telephone, and discussion forums. Both at present and in the foreseeable future, mHealth has shown great potential for development in all kinds of medical scenarios, whether it is in the prognosis and management of chronic diseases, or the construction of rapid treatment solutions for sudden illnesses, which can efficiently realize the deployment of medical resources. In addition, mHealth is more affordable than traditional doctor-patient scenarios, with time and geographic costs close to zero for patients, as evidenced by studies of primary care self-management behaviors related to chronic diseases. However, more authoritative health theories have not been widely applied as theoretical guides for health interventions in common mHealth research, especially in the cancer patient population, which is in greater need of postoperative health care. This study will explore the application of MTM theoretical modeling as a guide for health intervention research in the DTC patient population, with the aim of evaluating MTM-based intervention programs for clinical outcome improvement in DTC patients, as well as determining the effectiveness of MTM-based intervention programs in improving self-management skills in DTC patients. This study is conducive to filling the research gap of postoperative health management of Chinese DTC patients after being guided by health-based theories.

For patients with DTC, especially those who are at high risk of recurrence as determined by the postoperative risk factor stratification, it is especially crucial for them to actively cooperate with the doctor’s prescription for continuous TSH-suppressing endocrine therapy and self-health management after postoperative iodine 131 treatment. However, given that the mortality rate of differentiated thyroid cancer is very low compared with other types of cancer, patients may become lax in the prognosis process, especially the insufficient control of iodine-containing foods in their daily diets, or the erroneous consumption of other foods or beverages that may have an impact on the TSH-inhibiting drugs, which may have a great negative impact on the therapeutic effect. Therefore, it is important to explore more effective ways to improve patients’ self-management in the context of the current information age. In public health research, most mHealth interventions have been helpful in improving patients’ self-management, but there is no research on self-management of DTC patients in the context of mHealth. After combining mHealth, we selected the fourth-generation MTM model, which is a guiding significance for health intervention research in the international frontiers, to improve our intervention pathway and transform the theory into practice. Meanwhile, the application of MTM model in China is in the preliminary stage of exploration, and this study will fill the gap in this direction and provide new ideas for health management programs related to cancer prognosis and rehabilitation. The results of this study will show whether the application of health theory modeling based on health theory combined with mHealth application for disease prognosis health management model is feasible as well as effective, and provide policy recommendations and technical translation for the development of the application of mobility health management in the field of health management.

## Ethics statement

The study has been approved by the Ethics Committee of the Fourth Affiliated Hospital of Harbin Medical University, Harbin, Heilongjiang Province (2022-WZYSLLSC-20), and the registration of the study protocol with the China Clinical Trial Registry (ChiCTR2200064321) has also been completed. The participants provided their written informed consent to participate in this study.

## Glossary

5

**Table tab3:** 

DTC	Differentiated thyroid cancer
MTM	Multi-theory model of health behavior change
PD	Participatory Dialog
BC	Behavioral Confidence
CPE	Changes in Physical Environment
ET	Emotional Transformation
PC	Practice for Change
CSE	Changes in Social Environment
mHealth	Mobile health
T4	Thyroxine
T3	Triiodothyronine
TTM	Transtheoretical model
DMC	The Data Monitoring Committee
SAEs	All adverse events
AEs	Adverse events
CSQ-3	The Customer Satisfaction Questionnaire
EQ-5D-5L	The EuroQol-5 Dimensions 5 Levels
ARMS-7	The Renewal or Medication Adherence Scale
FFQ	The Food Frequency Questionnaire
I-FFQ	The Iodine-containing Food Frequency Questionnaire
HRP	Horseradish peroxidase
ELISA	Enzyme-linked immunosorbent assay
HPV	Human papilloma virus
mCi	Meters Curie
FT4	Free thyroxine
FT3	Free triiodothyronine
RIA	Radioimmunoassay
PHQ-4	A simplified version of the Anxiety Depression Scale
FCR-4	The Fear of Cancer Recurrence Scale
